### Sample size

The formula employed for the sample size estimation is: N = 2S

(

+

/

^(36)^

where N is sample size

sd is standard deviation; estimated to be 20·1 μg/l for serum ferritin^(37)^ and 1·2 g/dl for Hb (anaemia)^(32)^.

 = 1·96 (From Z table) at a precision of 5 % and CI of 95 %.

 = 0·84 (From Z table) at 80 % power.

d is effect size; estimated to be 9·4 μg/l for serum ferritin^(38)^ and 0·65 g/dl for Hb (anaemia)^(39)^.

Sample size (Serum ferritin): N = 2

(

*+*

*/*

= 72

Sample size (Hb): N = 2

(

*+*

*/*

= 53

The larger sample size (N = 72) of the 2 variables (serum ferritin and Hb) will be used for the study.

As a cluster randomised controlled trial, cluster design effect has to be considered in the sample size calculation to improve the power and precision of the study^(40,41)^. The required sample size for a cluster randomisation trial is obtained by multiplying the sample size of the individual randomisation trial (N = 72) by the design effect^(42,43)^. Design effect = 1 + intra-cluster correlation (m-1), where m is the average cluster size. An estimated intra-cluster correlation of 0·0009^(44)^ will be used. The average size of each cluster (school) in the study district is estimated to be 55 adolescent girls, with the number of anaemic adolescent girls in each school estimated to be 43^(32)^, thus m = 43. Design effect = 1 + 0·0009(43–1) = 1·037. Hence, considering the design effect of 1·037 and 15 % attrition rate, the sample size will be 86 participants per arm (258 participants for the 3 arms, with 43 participants to be chosen from each school).

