### Outcome measures

The primary outcomes will be serum ferritin (ug/l) and Hb (g/dl) concentrations of participants. Secondary outcomes will be prevalence of Fe deficiency, Fe deficiency anaemia and BMI-for-age.

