### Statistical analysis

Data analysis will be done using Statistical Package for Social Sciences version 22 and WHO AnthroPlus software. Shapiro–Wilk and Kolmogorov–Smirnov tests will be done to test quantitative data for normality. Data that turns out not to be normally distributed will be analysed using non-parametric tests. Continuous data will be reported as means and sd, whilst categorical variables will be presented as frequencies and percentages. Data will be analysed using intention to treat analysis. One-way ANOVA will be used to compare means of serum ferritin and Hb levels among the three study groups (arms). Tukey’s post hoc test of one-way ANOVA will be performed to determine intergroup differences. Paired *t* test will be used to determine change in means of serum ferritin and Hb levels within groups (baseline and end-line). Relationship between covariates and outcome variables will be determined using multivariate linear and binary logistic regression analyses. WHO AnthroPlus software will be used to compute BMI-for-age Z-scores to determine participant’s nutritional status. Missing data will be resolved via multiple imputations. *P* < 0·05 will be considered significant at two-tailed tests.

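### The 80 % power claimed for ferritin is for one two-arm test at z = 1.96; under the declared three-pair Tukey test it is about 67 % (Hb keeps about 81 %)

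*Protocol article*

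**What the plan says.** The Sample size section uses a two-group formula for means. The first z value is given as "1·96 (From Z table) at a precision of 5 % and CI of 95" per cent, and the second as "0·84 (From Z table) at 80 % power". For ferritin, "sd is standard deviation; estimated to be 20·1" μg/l and "d is effect size; estimated to be 9·4" μg/l. For Hb the SD is 1.2 g/dl and the effect 0.65 g/dl. The results are 72 and 53 per arm, and "The larger sample size (N = 72) of the 2 variables (serum ferritin and Hb) will be used for the study". A design effect of 1.037 and 15 % attrition bring this to 86 per arm.

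The Statistical analysis section declares a one-way ANOVA over the three arms for each outcome, and "Tukey’s post hoc test of one-way ANOVA will be performed to determine intergroup differences". Significance is P < 0.05, two-tailed. Under Outcome measures, "The primary outcomes will be serum ferritin (ug/l) and Hb (g/dl) concentrations of participants".

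The end of the introduction states two hypotheses. The first is that the fortified beverage is better than the unfortified one (arm 1 against arm 2). The second is that it does at least as well as iron-folate (arm 1 against arm 3). Arm 2 against arm 3 appears in neither.

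**The concern.** The calculation and the test belong to different designs. The formula buys 80 % power for one comparison with the whole 5 % spent on it. Tukey's procedure holds 5 % over all three pairs, so each pair faces a higher hurdle. Some of that protection goes to arm 2 against arm 3, about which the protocol asks nothing, and the main efficacy question pays for it.

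At stake is the chance of missing the effect that the trial was sized to find. Ferritin fixed the sample size and has no reserve, so the whole loss falls on it.

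A smaller question is what counts as success with two primary outcomes. The article does not say whether one or both must be significant. The answer decides whether the issue is error or power.

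**Working it through.** **Inputs**, all from the Sample size section: SD 20.1 and effect 9.4 μg/l (ferritin); SD 1.2 and effect 0.65 g/dl (Hb); z values 1.96 and 0.84; ICC 0.0009; cluster size 43; attrition 15 %.

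**Step 1. The protocol's own figures.** n = 2·SD²·(1.96 + 0.84)²/d².
- Ferritin: 2 × 20.1² × 2.8²/9.4² = 71.7, so 72, as stated.
- Hb: 2 × 1.2² × 2.8²/0.65² = 53.4 (stated as 53).
- Design effect: 1 + 0.0009 × 42 = 1.0378. Then 72 × 1.0378 × 1.15 = 85.9, so 86, as stated.

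The stated sizes are therefore those of a single unadjusted two-arm test.

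**Step 2. The hurdle under the declared test.** With three arms of 72 there are 3 × 72 − 3 = 213 degrees of freedom. Tukey's critical value for a pair is q(0.95; 3, 213)/√2 = 2.36, which corresponds to a per-pair two-sided level of about 0.019.

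**Step 3. Power for one pair at 72 per arm.** The standardised effect is d/(SD·√(2/n)).
- Ferritin: 9.4/(20.1 × √(2/72)) = 2.806. Against 1.96, Φ(2.806 − 1.96) = 80.1 %. Against Tukey, the noncentral t gives 67.2 % (normal approximation 67.8 %; Bonferroni over three pairs 66.0 %).
- Hb: 0.65/(1.2 × √(2/72)) = 3.25. Against 1.96, 90.1 %. Against Tukey, 81.2 %.

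**Step 4. Sensitivity to the number analysed.**

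| Effective n per arm | Ferritin, z = 1.96 | Ferritin, Tukey | Hb, Tukey |
|---|---|---|---|
| 72 | 80.1 % | 67.2 % | 81.2 % |
| 86 × 0.85/1.0378 = 70.4 | 79.3 % | 66.1 % | 80.3 % |
| 86/1.0378 = 82.9 (no attrition) | 85.3 % | 74.2 % | 87.0 % |
| 86 (no attrition, no design effect) | 86.6 % | 76.0 % | 88.3 % |

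**Step 5. Size needed for 80 % on ferritin with Tukey.** With the large-sample critical value 2.344: 2 × 20.1² × (2.344 + 0.842)²/9.4² ≈ 92.8, so about 93 per arm before inflation. Then 92.8 × 1.0378 = 96.3. This becomes 111 per arm with the protocol's ×1.15, or 114 if divided by 0.85, against 86 planned.

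**Step 6. Two primary outcomes.** Tukey holds 5 % over the pairs within each outcome. If a win on either outcome counts, the error across the two is at most 5 % + 5 % = 10 %, and 1 − 0.95² = 9.75 % if they are independent. If both must be significant there is no inflation. Joint power for a pair under Tukey then cannot exceed ferritin's 67 %, and would be 0.672 × 0.812 = 55 % if the outcomes were independent.

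**The case against.** Tukey after a three-arm ANOVA is a valid and conservative choice. Covering a pair that nobody asked about is inefficient but not an error. That stands: the defect is the mismatch with the sample size, not the use of Tukey.

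A reader might infer that the trial as a whole has 67 % power. The figures do not support that. Hb, the other primary outcome, keeps about 80–81 % because ferritin set a larger size than Hb needs. Nor does having two primary outcomes cause any of the loss; it comes from Tukey's critical value alone.

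The 67 % is also conditional. Non-normal data are to go to non-parametric tests, so it applies only if ferritin passes the normality checks. The plan declares intention to treat with multiple imputation, so one could argue for using all 86 per arm. Imputation does not restore the information that is lost, so 74–76 % is an upper limit, and it is still below 80 %.

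A reader might further infer that the plan lets the false-positive rate nearly double. The article does not say that either outcome suffices. The hypotheses speak of iron and Hb status together, which can equally be read as requiring both, and then nothing is inflated. A rule for combining two primary outcomes may also sit in a fuller document. This part is therefore a request to state the rule, not a demonstrated error.

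**Conclusion.** The sizing and the declared pairwise test do not match. On the protocol's own SD, effect and design effect, ferritin power for one pair is about 67 % instead of 80 %, within a range of 66 % (15 % attrition and the design effect) to 76 % (all 86 analysed, no design effect). No scenario examined reaches 80 %. Hb is adequately powered under Tukey.

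These figures assume a parametric analysis of ferritin. They take the very small ICC at face value and use participant-level degrees of freedom, although there are only two schools per arm. They isolate the effect of the Tukey choice and do not forecast the trial's real power.

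The up-to-10 % error across outcomes holds only under an either-outcome rule, which the article does not state. The mismatch does not invalidate the trial, but the stated power is wrong for the declared test and should be corrected.

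**What to change.** Choose one of two wordings before the analyst learns the allocation.

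1. **Align the test with the formula.** Name arm 1 against arm 2, the first hypothesis, as the primary contrast for each outcome, tested at two-sided 5 % without Tukey. Make the other two pairs secondary. This restores the 80 % that the formula assumed and needs no more participants. The cost is that the other pairs lose equal confirmatory status, including arm 1 against arm 3, which the second hypothesis concerns. A difference test on that pair could not show similarity in any case.
2. **Keep Tukey and restate the power.** Give about 67 % for ferritin and about 81 % for Hb at 72 per arm, with a note that these rest on the protocol's stated inputs. The cost is an openly lower power for the outcome that set the size.

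Under either option, add one sentence saying whether one or both primary outcomes must be significant. If either suffices, adjust across them, for example by Holm. At its first step (2.5 %) with 72 per arm, power for the single unadjusted contrast is 71 % for ferritin and 84 % for Hb; with Tukey kept it is 57 % and 73 %. If both are required, no adjustment is needed, but joint power should be stated. A fixed order (ferritin, then Hb) would keep ferritin at the full 5 %. It would also make Hb depend on the weaker outcome: with option 1, Hb is won with probability 0.801 × 0.901 = 72 % if the outcomes are independent, and at most 80 %. That trade-off is for the sponsor to weigh.

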## Methods

### Study design

The study will be a three-arm parallel cluster randomised controlled trial. Participants in arm 1 (Intervention group) will receive pearl millet beverage enriched with baobab pulp, while participants in arm 2 (Control group 1) will receive unfortified pearl millet beverage, once a day, five times a week, for six months. Participants in arm 3 (Control group 2) will receive weekly Fe -folate supplementation also for six months. The study outcomes will be assessed twice, at baseline and end-line.

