### Inclusion criteria

Adolescent girls aged 10–19 years who have mild or moderate anaemia (8 < Hb < 12 g/dl for girls aged ≥ 12 years and 8 < Hb < 11·5 g/dl for girls aged < 12 years) and consent to participate will be included in the study.

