#### Deworming

All participants will be treated against intestinal parasites by the study physician using a single dose of albendazole 400 mg chewable tablets. The first dose will be given 2 weeks prior to the commencement of feeding and a second dose given at midpoint of the intervention^(70)^.

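### Arms are compared on raw ferritin and Hb with no stated baseline term; baseline is expressly used only in within-arm paired t tests, which address neither hypothesis

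*Protocol article*

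**What the plan says.** The Outcome measures section states: "The primary outcomes will be serum ferritin (ug/l) and Hb (g/dl) concentrations of participants". The Study design section adds: "The study outcomes will be assessed twice, at baseline and end-line". A baseline value of each primary outcome is therefore planned for every girl.

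For the comparison of arms, the Statistical analysis section says: "One-way ANOVA will be used to compare means of serum ferritin and Hb levels among the three study groups (arms"). Pairwise comparisons come from the same analysis, since Tukey's "post hoc test of one-way ANOVA will be performed to determine intergroup differences". No baseline term is given and no time point is named. Baseline values are named only in the next step, where the paired t "test will be used to determine change in means of serum ferritin and Hb levels within groups (baseline and end-line"). The Abstract repeats this split: ANOVA among groups, paired t test within groups.

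One more sentence could bear on the matter: "Relationship between covariates and outcome variables will be determined using multivariate linear and binary logistic regression analyses". It names neither the baseline value nor arm, and it is not presented as the treatment comparison.

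Three other places matter. The Inclusion criteria admit "Adolescent girls aged 10–19 years who have mild or moderate anaemia". The Deworming section says: "All participants will be treated against intestinal parasites by the study physician"; the malaria section likewise has all participants tested, and positives treated. Table 1 shows one pre-treatment Hb, in the enrolment column.

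**The concern.** The hypotheses at the end of the introduction are both comparative: fortified against unfortified beverage, and fortified beverage against iron-folate. A test of change inside one arm addresses neither. A small P value in one arm beside a larger one in another is not a test of the difference between them.

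The within-arm Hb tests also start from a tilted position. Girls enter because their Hb is low, so part of the low reading is transient and the mean should rise on re-measurement. Co-treatments given in every arm may add to that rise. A within-arm P value can then be small with no product effect.

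Meanwhile the between-arm analysis does not use the one covariate most likely to predict the end-line value. That costs precision and leaves any chance baseline difference in the estimate. With two schools per arm, randomisation gives little protection against such differences.

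**Working it through.** **Inputs from the protocol article.** SD 20.1 µg/l (ferritin) and 1.2 g/dl (Hb); effects 9.4 µg/l and 0.65 g/dl; ICC 0.0009, cluster size 43, attrition 15% (Sample size). District anaemia prevalence 75% (Study area). Entry range 8 to 12 g/dl for girls aged 12 or more (Inclusion criteria), applied here to all ages. Two schools per arm (Randomisation). The baseline/end-line correlation r is not given; it is assumed and shown as a range.

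**The plan's own figures.**
- Ferritin: 2 × (20.1 × 2.80 / 9.4)² = 71.7, so 72, as stated.
- Hb: 2 × (1.2 × 2.80 / 0.65)² = 53.4; the plan gives 53.
- Design effect: 1 + 0.0009 × 42 = 1.0378. Then 72 × 1.0378 × 1.15 = 85.9, so 86 per arm, as stated.
- Completers: 86 × 0.85 = 73 per arm.

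**Regression to the mean in Hb, no treatment effect, screening Hb taken as baseline.**
- Population mean with 75% below 12: 12 − 0.674 × 1.2 = 11.19 g/dl.
- Normal distribution truncated to 8–12: mean 10.70, SD 0.85.
- Expected rise = (1 − r) × (11.19 − 10.70).
- SD of change = √[(1 − r)² × 0.85² + (1 − r²) × 1.2²].
- Probability of a significant rise: noncentral t, n = 73, two-sided 0.05. With no drift, the upper tail is 2.5%.

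| Population r | Expected rise (g/dl) | Share of 0.65 | SD of change | Significant rise |
|---|---|---|---|---|
| 0.5 | 0.25 | 38% | 1.12 | 46% |
| 0.7 | 0.15 | 23% | 0.89 | 29% |
| 0.9 | 0.05 | 8% | 0.53 | 12% |

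At 64% prevalence the rises are 0.35, 0.21 and 0.07 g/dl, and the probabilities about 75%, 51% and 20%. Any effect of deworming or malaria treatment would come on top.

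**Precision gained by baseline adjustment, girl level, ignoring clustering.** Residual variance falls by the square of the correlation among enrolled girls.

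- *Hb.* Selection narrows the baseline SD from 1.2 to 0.85, which lowers the correlation among enrolled girls: r_s = r × 0.85 / √[r² × 0.85² + (1 − r²) × 1.2²].
  - r = 0.5: r_s = 0.38, variance down 14%, 73 girls act like 73 / 0.856 = 85.
  - r = 0.7: r_s = 0.57, variance down 33%, 73 girls act like 73 / 0.674 = 108.
- *Ferritin.* It is not the selection variable. If the correlation among enrolled girls is 0.5 or 0.7, the variance falls by 0.5² = 25% or 0.7² = 49%.

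**The case against.** The strongest reply is that the named between-arm test is valid. Schools are randomised, so an unadjusted end-line comparison is unbiased in expectation. Selection on Hb, deworming and malaria treatment apply to all three arms, so they do not distort the contrast. The protocol never says it will judge efficacy from within-arm P values. All of this stands. A reader might infer that baseline imbalance biases the arm comparison, or that the trial plans to claim efficacy from the paired tests; the text supports neither. The cost is precision and exposure to chance imbalance, plus tests that invite misreading.

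Second, the regression sentence names no covariates and the ANOVA sentence no time point, so baseline adjustment is not ruled out. True, but the article names its treatment comparison, and baseline is not in it. This is a stated choice, not a detail left open.

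Third, the drift calculation needs the screening Hb to be the baseline Hb. Table 1 suggests this but does not settle it: the sampling section screens all girls and then selects among those eligible, and a venous sample is described at baseline. A separate baseline draw would remove part of the shift.

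Fourth, it is tempting to extend the upward drift to ferritin. The documents do not support that. Ferritin is not the entry criterion, and the Baseline assessment section notes that it needs adjusting for inflammation, so treating infection could lower it.

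Fifth, applying r = 0.5 or 0.7 directly to enrolled girls would put the Hb gain at 97 or 143 effective girls. If these are population correlations, as in the drift calculation, that ignores the narrowed baseline range and is too large.

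**Conclusion.** The point holds as an avoidable weakness in the analysis, not as a bias in the randomised comparison. The between-arm test has no stated baseline term, and the one analysis that expressly uses baseline answers neither hypothesis.

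For Hb, an upward within-arm drift without product effect is expected. Its size, about 0.05 to 0.25 g/dl with a 12% to 46% chance of a significant rise in an untreated arm of 73, rests on 75% prevalence, a normal distribution, assumed population correlations of 0.9 to 0.5, and the screening value serving as baseline. For ferritin, no direction is claimed.

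The girl-level gain from adjustment is moderate for Hb (14% or 33% less residual variance at population r = 0.5 or 0.7) and possibly larger for ferritin (25% or 49% if the correlation among enrolled girls is 0.5 or 0.7). These figures ignore clustering, so they should not be read as gains of the same size at arm level.

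**What to change.** Make the primary estimate for each outcome the baseline-adjusted difference between arms at end-line: regress the end-line value on arm and the girl's own baseline value of the same outcome, and take the pairwise contrasts from that model. Report within-arm change descriptively, with a sentence that it is not evidence of efficacy.

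Handle clustering in the same analysis, with school as a random effect or by a cluster-level analysis, using small-sample degrees of freedom. School cannot be a fixed effect, because each school lies wholly within one arm.

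The cost is small: the data are already planned, and the change is to the analysis text, to be made before any unblinded analysis. It is not free of limits. Six schools in three arms leave about 6 − 3 = 3 between-school degrees of freedom, and baseline adjustment does not remove that constraint.

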### Data monitoring

The dietary intervention, which participants are accustomed to, and the other assessments pose minimal risk to participants. As such, a steering committee will not be formed, since no severe adverse events are anticipated. The principal investigator, the study physician and the other study investigators will regularly monitor for adverse effects and progress of the trial.

### Adverse events

Though the risks of partaking in this feeding trial are low, all participants will be monitored and any suspected adverse events will be attended to by the study physician. The study physician will assess participants every week for any adverse events. Participants will also be provided with the contact information of the lead investigator and study physician to allow for rapid reporting of adverse reactions. All adverse events will be documented in the daily case report form and reported regularly to the ethics committee.

### Ethics and dissemination

This study will be conducted according to the guidelines laid down in the Declaration of Helsinki, and all procedures involving human subjects/patients were approved by the Committee on Human Research, Publications and Ethics (CHRPE/AP/279/23) at Kwame Nkrumah University of Science and Technology, Ghana. Written consent of participants and their guardians will be obtained by research assistants. Prior to the consent taking, the researchers will provide the participants and their guardians with enough information about the study including risks and benefits and assure them of confidentiality. Partaking in the study will be made voluntary and respondents can choose to withdraw from the research at any time. The trial is registered with the Pan African Clinical Trial Registry (https://pactr.samrc.ac.za/), with registration number PACTR202306743290094 and a version date of February 16, 2024. The protocol is written based on Standard Protocol Items: Recommendations for Interventional Trials guidelines^(73)^. To maintain confidentiality, code numbers will be assigned to all participants; hence, no name will be recorded. Data collected will be stored appropriately, locked and accessible to only the researchers. Any changes to the protocol will be communicated to the ethics committee and funder for approval prior to implementation. Study findings will be disseminated through peer-reviewed publications, with copies placed in Kwame Nkrumah University of Science and Technology’s libraries. Additionally, copies will also be placed at the Kumbungu District Education Office and Kumbungu District Health Directorate. The principal investigator will manage authorship based on the study team’s tasks and there is no intention to use professional writers. The trial data and informed consent materials will be made available on reasonable request from the principal investigator; however, personally identifiable information will not be released.

